**Influence of cardiopulmonary bypass pump on selenium status of cardiac surgical patients, undergoing coronary artery bypass surgery.**

*Inclusion criteria:*

100 patients, undergoing open heart surgery should be included in the trial. Here, 50 patients will be operated conventional, with the use of CPB and cardioplegia. Further 50 patients will be operated on the beating heart, without the use of CPB (OPCAB= „off pump coronary artery bypass“). The surgeon ([name]) will perform the surgery in all patients.

Included will be all patients suffering from a coronary 3-vessels heart disease. They will undergo surgery in general anaesthesia with median sternotomia in the case of elective or urgent indication for treatment. Patients should be free of further serious cardiac diagnoses (valve-disease, aneurysms etc.). Excluded are patients with ischemic cardiomyopathy. The aimed revascularization should be completely performed and conducted by one surgeon. 50 patients are undergoing conventional surgery, with the use of cardiopulmonary bypass (CPB), with moderate hypothermia and cardioplegic cardiac arrest. The other 50 patients will be treated without the use of CPB (OPCAB).

Only adults, after written informed consent for the study participation will be included.

*Exclusion criteria:*

Excluded will be patients with emergency surgery (NSTEMI or STEMI), patients with ischemic cardiomyopathy or additional cardiac diagnoses (valve-diseases or aneurysms), patients incapable of giving consent, pregnant patients and women with childbearing potential, in which pregnancy cannot be excluded.

Patients will be enrolled in the clinical trial, after patient information, at least, the evening before the operation.

*Methodology of study:*

After induction of anaesthesia, within one hour after admission the patient to the intensive care unit and every further morning on the intensive care unit or intermediate care unit (IMC), 10 ml blood will be drawn from the central venous line, placed independently of the study for the operation. A separately puncture for this purpose it is not necessary.

Selenium values will be measured from this blood in the whole blood sample by electrothermal atomic absorption spectroscopy.

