Beside this, the following parameters will be measured daily in the routinely diagnostic and later correlated with the selenium concentration at the respective time points. The measurement of glutathione peroxidase (GPX) und thioredoxin (TRX) reductase will be conducted in the laboratory of the company Biosyn. The „macrophage migration inhibitory factor (MIF)“ will be determinated from the remaining blood.

*Determinated parameters:*

- Procalcitonin
- CRP
- IL-6, IL-10
- Leukozyten
- Glutathione peroxidase (GPX)
- Asymmetric dimethylarginin (ADMA)
- Thioredoxin reductase (TRX)
- Platelets
- Bilirubin
- Creatinine
- Lactat
- Albumine
- AT-III
- CK, CKMB and troponin
- Duration of mechanical ventilation
- Duration of hospitalisation
- SOFA-Score
- SAPS-Score

All blood samples will be kept until study end and their analysis (max. 24 months) and will be disposed thereafter.

Values of selenium, markers of oxidative stress (GPX, ADMA) and inflammation (IL-6, IL-10) from the 1.POD on will be used for possible long-term analyses of selenium course.

All data will be recorded on a documentation form.

*Study duration:*

The study will be terminated, as 100 patients are included or after a maximum of 24 months.

*Risks:*

Patients are not exposed to additional risk by blood sampling before surgery, after admission to intensive care unit, and every further day on the intensive care unit. All blood samples will be drawn from catheter, placed independently of study participation, for cardiovascular monitoring. Therefore blood sampling for this study is not associated with pain.

Summarized, according to current scientific evidence there is not expected an impairment or additional stress for the participating patients.

*Benefits:*

There is no benefit for the individual participant of the study expected.

Significant low selenium values (lower than the reference value of selenium in whole blood of 100-140µg/L) will be detected.

*Statistic:*

All data will be recorded pseudonymized and analyzed anonymized.

Recorded patient data will be anonymized, by numbering in order of study inclusion. Thereafter the mean and standard deviation of the recorded data will be calculated and this data will be further statistically evaluated.

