Hereby the correlation of measured selenium blood values and laboratory chemical parameters of inflammation and the clinical patient outcome will be evaluated. Differences between the groups (OPCAB vs. conventional CPB-surgery) concerning the laboratory chemical and clinical course will be statistically analyzed by tests comparing independent groups. Correlations between the different variables will be analyzed by the methods of Pearson and Spearman-rho. The predictive value of selenium blood levels concerning certain outcome parameters will be determined by the receiver-operating characteristic curves (ROC).

*Quality assurance:*

This observational study will be conducted under the Good Clinical Practice guidelines.

*Adresses and responsibilities:*

Scientific direction:

PD [name]

Senior consultant

Department of Anaesthesiology

University Hospital Aachen

[name]

[name]

Direct line - [contact]

[contact] (secretariat)

[contact]

E-Mail: [contact]

Involved physicians:

[name], Senior consultant, Department of Thoracic, Cardiac and Vascular Surgery

[name] (direct line: [name]), resident physician, Department of Anaesthesiology

Laboratory:

biosyn Arzneimittel GmbH

[name]

[name]

Telefon: [name]

Telefax: [name]

[contact]

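### The protocol names only unadjusted independent-group tests for CPB versus OPCAB and states no use of the pre-surgery selenium value taken in every patient

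*Protocol*

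**What the plan says.** The title asks how the bypass pump influences selenium status. Under Inclusion criteria, "50 patients will be operated conventional, with the use of CPB and cardioplegia", and a further 50 are operated on the beating heart without CPB. No random allocation is described, and Quality assurance states: "This observational study will be conducted under the Good Clinical Practice guidelines".

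Methodology of study sets the blood draws: "After induction of anaesthesia, within one hour after admission the patient to the intensive care unit and every further morning" on the intensive or intermediate care unit. Selenium is measured in that blood. The Risks section confirms the order of events, referring to "blood sampling before surgery, after admission to intensive care unit, and every further day on the intensive care unit". So a selenium value from before exposure to bypass is planned for every patient.

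For the group comparison, the Statistic section says that differences "concerning the laboratory chemical and clinical course will be statistically analyzed by tests comparing independent groups". The other analyses it names are means and standard deviations, Pearson and Spearman correlations, and ROC curves. None is described as using the post-induction value as a covariate, in a change score or in a repeated-measures model. A sentence under Determinated parameters adds that selenium, GPX, ADMA, IL-6 and IL-10 values "from the 1.POD on will be used for possible long-term analyses of selenium course".

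**The concern.** The title question is about change caused by bypass. A comparison of postoperative values alone answers who has lower selenium afterwards. In a randomised trial the two questions agree in expectation. Here technique is not randomised, so nothing in the design makes the groups alike in selenium before surgery. A baseline gap would carry over in part to the postoperative values and could imitate a CPB effect or, in the other direction, hide one.

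The second loss is precision. If a patient's selenium before surgery predicts the value afterwards, a test that leaves it out keeps avoidable variance in the comparison.

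This is more than a detail left to a later analysis plan. The protocol names the class of test for its main comparison, and an analysis plan that followed the wording would be unadjusted.

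**Working it through.** **Inputs from the protocol.** 50 CPB and 50 OPCAB patients (Inclusion criteria); selenium after induction, within one hour of ICU admission and each further morning (Methodology of study). The sample size comes with no alpha, power, effect or SD, so there is no planned figure to reproduce.

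**Assumptions.** Two-sided alpha 0.05, 80% power, no dropout, effects in units of the postoperative SD, normal approximation. The correlation ρ between baseline and postoperative selenium is taken from 0.3 to 0.8, and the true baseline gap b as 0.2, 0.3 or 0.5 SD.

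**Precision.** The unadjusted standard error is √(2/50) = 0.20 SD. The detectable difference is (1.960 + 0.842) × 0.20 = 0.56 SD (0.57 with the t distribution). Adjustment multiplies the variance by 1 − ρ², and a change score multiplies it by 2(1 − ρ).

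| ρ | 1 − ρ² | Detectable difference, adjusted | Power for 0.5 SD, adjusted | Unadjusted n per group of equal precision, 50/(1 − ρ²) | 2(1 − ρ), change score |
|---|---|---|---|---|---|
| 0.3 | 0.91 | 0.53 SD | 75% | 55 | 1.40 |
| 0.5 | 0.75 | 0.49 SD | 82% | 67 | 1.00 |
| 0.7 | 0.51 | 0.40 SD | 94% | 98 | 0.60 |
| 0.8 | 0.36 | 0.34 SD | 99% | 139 | 0.40 |

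Unadjusted power for 0.5 SD is 71%. The adjusted figures assume similar baselines; a gap of b inflates the adjusted variance by about 1 + b²/4, which is 1.02 at 0.3 SD and 1.06 at 0.5 SD.

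**Bias.** Suppose CPB has no effect and the postoperative value regresses on baseline. A gap b then appears postoperatively as ρb. With s = ρb/0.20, the false-positive rate of a test on postoperative values is Φ(−1.96 − s) + Φ(s − 1.96). For ρ = 0.7 and b = 0.3: s = 0.21/0.20 = 1.05, and the rate is Φ(−3.01) + Φ(−0.91) ≈ 0.18.

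| ρ | b = 0.2 | b = 0.3 | b = 0.5 |
|---|---|---|---|
| 0.5 | 8% | 12% | 24% |
| 0.7 | 11% | 18% | 42% |
| 0.8 | 13% | 22% | 52% |

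**Simulation check** (4,000 studies per setting, ρ = 0.7, no CPB effect): false-positive rates by method.

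| Gap b | Postoperative values only | Baseline-adjusted | Change score |
|---|---|---|---|
| 0 | 4.7% | 4.8% | 4.9% |
| 0.3 SD | 17% | 4.7% | 8.4% |
| 0.5 SD | 41% | 5.0% | 15% |

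**The case against.** **The protocol does not say which quantity is tested.** A reader might infer that the baseline is deliberately discarded. The text does not support that: it is silent, and an independent-group test could be run on change from the post-induction value. What stands is that no use of the baseline is stated. A change score would also be only a partial remedy, since it gains no precision at ρ = 0.5 and loses some below that.

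**The sentence on values from the first postoperative day** might be read as shutting the baseline out. It only says which values feed a possible further analysis. It does not rule the post-induction value out as a covariate there or in the group comparison.

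**Other markers.** A reader might infer a pre-surgery value for GPX, TRX, ADMA and the cytokines too. The protocol says only that these are measured daily and correlated with selenium at matching times, which suggests a shared first sample without stating it. Markers that are low before surgery may also predict the postoperative rise poorly. Ventilation time and hospital stay have no baseline at all. The point is therefore secure for selenium only.

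**Adjustment does not settle bias in non-randomised groups.** This stands. The roughly 5% rates above hold because the simulated baseline carries the whole group difference. If instead a stable 0.3 SD gap is measured with reliability 0.7, adjustment leaves 0.3 × (1 − 0.7) = 0.09 SD of bias. The standard error is 0.20 × √0.51 = 0.14 SD, and the false-positive rate is near 10%. A change score would be unbiased in that setting, while the test on postoperative values alone would reject in about 32% of studies. Confounding through other reasons for choosing a technique is untouched.

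**A gap would be visible** in the planned means and SDs. It would be seen but not removed. A true 0.3 SD gap is 0.3/0.20 = 1.5 standard errors, which a 5% test would flag in only about 32% of studies.

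**Conclusion.** The point holds for selenium and should be fixed. The one between-group method named is unadjusted, the groups are not randomised, and a pre-surgery value planned for every patient has no stated role. Adjustment would lower the detectable difference from about 0.56 SD to between 0.53 and 0.34 SD for ρ from 0.3 to 0.8. At ρ = 0.3 that is a modest gain of 9% of variance; at ρ = 0.7 it is worth 98 rather than 50 patients per group. The 18% false-positive rate needs a real 0.3 SD gap at ρ = 0.7. The protocol gives no sign of such a gap and no value for ρ, so these figures show what could happen and are not estimates for this study. The direction of the precision gain holds for any nonzero ρ. The documents do not support concluding that the comparison is invalid as it stands, or that baseline adjustment alone would make it causal.

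**What to change.** In the Statistic section:

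- For selenium, make the CPB versus OPCAB analysis a linear model of the postoperative value (ICU admission, first postoperative day and later) on technique plus the patient's own post-induction selenium. Report the adjusted difference with its 95% confidence interval.
- Show change from the post-induction value as a sensitivity analysis, because the two methods rest on different assumptions about a baseline gap. Keep the raw comparison as descriptive.
- Apply the same model to other laboratory markers only where a post-induction value exists, and say which these are. Transform skewed markers where needed.
- State that adjustment for baseline selenium does not remove other confounding by choice of technique.

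For selenium this costs wording only: no new samples, patients or procedures. For the other markers, it must first be confirmed that the post-induction sample is assayed for them.

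### Selenium correlations are planned with simple coefficients that leave out surgical technique, so after surgery a CPB effect on both variables could pass for a selenium association

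*Protocol*

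**What the plan says.** The protocol's title gives the question: "Influence of cardiopulmonary bypass pump on selenium status of cardiac surgical patients". Under Inclusion criteria there are two groups of equal size: "50 patients will be operated conventional, with the use of CPB and cardioplegia", and "Further 50 patients will be operated on the beating heart, without the use of CPB". Quality assurance calls the study observational, and no randomisation is mentioned.

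Under Methodology of study, blood is drawn after induction of anaesthesia, within an hour of ICU admission, and each further morning in intensive or intermediate care. The other parameters are to be "later correlated with the selenium concentration at the respective time points".

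The Statistic section plans that "the correlation of measured selenium blood values and laboratory chemical parameters of inflammation and the clinical patient outcome will be evaluated". A separate sentence compares OPCAB with CPB on laboratory and clinical course by tests for independent groups. The next sentence gives the correlation method: "Correlations between the different variables will be analyzed by the methods of Pearson and Spearman-rho".

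The section does not mention stratification by technique, partial correlation or regression. It does not say which coefficient applies to which pair. It gives no significance level and names no main correlation. It also does not say whether the correlations are run over both groups together.

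**The concern.** By its own question the study treats CPB as a possible cause of selenium change, and it plans to look for CPB/OPCAB differences in laboratory and clinical course. Technique is therefore a candidate common cause of both sides of the planned correlations. A Pearson or Spearman coefficient computed over both groups mixes the association within groups with the difference between them. If CPB lowers selenium and raises a marker such as IL-6, the two correlate negatively across all patients even if they are unrelated among CPB patients and unrelated among OPCAB patients.

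At stake is how the correlation results are read. A selenium-inflammation or selenium-outcome link could be reported that only restates which operation was done. The larger the CPB effect, the less an unadjusted correlation says about selenium itself.

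**Working it through.** The protocol gives no correlation, effect size or power figure to reproduce, so the check asks how large the distortion could be.

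**Inputs from the protocol.** 100 patients, 50 per technique (Inclusion criteria); bivariate Pearson and Spearman coefficients (Statistic).

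**Assumptions, because the protocol is silent.** Two-sided alpha 0.05; both groups analysed together; all 100 patients contributing at the time point; zero correlation within each group; CPB shifts selenium by -d and the marker by +d, in within-group SD units, with d from 0.3 to 1.5.

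**Step 1: pooled correlation.** With 1:1 groups the between-group covariance is 0.5 × 0.5 × (-d)(d) = -d²/4, and each variable's total variance is 1 + d²/4. Hence

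pooled r = -(d²/4) / (1 + d²/4).

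For d = 0.8: 0.16/1.16 = 0.138. For d = 1.0: 0.25/1.25 = 0.20. For d = 1.5: 0.5625/1.5625 = 0.36.

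**Step 2: chance of p<0.05.** By Fisher's z, let m = atanh(|r|) × √(100 - 3) = atanh(|r|) × 9.849. Then the chance is 1 - Φ(1.96 - m) + Φ(-1.96 - m). For d = 0.8: m = 0.1388 × 9.849 = 1.367, giving 27.7%.

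**Step 3: simulation.** 5,000 studies per shift with normal variables; "adjusted" below is the Pearson correlation after removing group means.

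| Shift d (SD) | Pooled \|r\| | p<0.05, Fisher z | p<0.05, simulated Pearson | p<0.05, simulated Spearman | p<0.05, adjusted |
|---|---|---|---|---|---|
| 0.3 | 0.02 | 5.5% | 5.2% | 5.2% | 4.8% |
| 0.5 | 0.06 | 8.9% | 8.8% | 8.8% | 5.4% |
| 0.8 | 0.14 | 27.7% | 29.0% | 28.8% | 4.8% |
| 1.0 | 0.20 | 51.5% | 53.0% | 54.2% | 5.2% |
| 1.5 | 0.36 | 96.0% | 97.3% | 98.0% | 5.3% |

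With a log-normal marker, unadjusted Pearson rejects less often (18.4%, 32.0% and 74.5% at d = 0.8, 1.0 and 1.5), while Spearman is almost unchanged (28.6%, 53.9%, 97.8%). Over both distributions the adjusted rate stays between 4.6% and 5.4%.

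**Step 4: what the size depends on.** With unequal shifts d₁ and d₂ the formula becomes |r| = (d₁d₂/4) / √[(1 + d₁²/4)(1 + d₂²/4)], which is zero if either shift is zero. CPB must affect both variables. On later days fewer patients remain in intensive or intermediate care; for a given shift and an even split, r is the same but the chance of p<0.05 is lower than in the table.

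**Step 5: the two coefficients.** With no CPB effect and n = 100 (20,000 simulated studies), at least one of Pearson and Spearman gives p<0.05 in 6.6% (both variables normal), 8.3% (one log-normal) or 8.7% (both log-normal). The ceiling, if the two tests were independent, would be 1 - 0.95² = 9.75%.

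**The case against.** The strongest reply is that pooling is inferred. The protocol does not say the correlations run over all patients together, and a statistical analysis plan that is not at hand could stratify. This stands, and it makes the point conditional. It does not remove the point, because the protocol names a method, and that method has no place for technique.

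Second, the protocol states no alpha and no confirmatory correlation, and a pooled correlation produced by CPB is a real marginal association. This also stands: the percentages describe how often a correlation would look significant without any link within technique, and they do not show a breach of a declared error rate. Adjustment would not hide a genuine link, because if low selenium itself drove inflammation, the association would also appear within each group.

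Third, no shift sizes are given, and at 0.3 to 0.5 SD little happens. That is correct. The title asks only about selenium, and the protocol plans to test for group differences in inflammation and outcome without predicting them.

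Several stronger readings are not supported:

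- A reader might infer that naming Pearson and Spearman gives every pair two chances of significance. The sentence can equally mean one method per variable type, which suits a list mixing laboratory values, SOFA and SAPS scores and durations. Nothing says the more favourable result will be chosen, and the inflation would be modest even then (Step 5).
- A reader might infer that days are pooled as if independent. Methodology of study already ties the correlations to the respective time points.
- A reader might extend the problem to every sample. The post-induction sample precedes CPB, so CPB cannot be the common cause there.

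**Conclusion.** The point holds as a conditional weakness with an inexpensive remedy. The simple coefficients named in the Statistic section cannot, over both groups together, separate a selenium association from the effect of the operation at ICU admission and later. On the stated assumptions the distortion is negligible at a shift of 0.3 SD, small at 0.5 SD and serious from about 0.8 SD, where roughly 28% of studies would show p<0.05 with no association inside either group. At 1.0 and 1.5 SD the figures are about 51% and 96%.

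The algebra is certain. Whether the groups will be pooled, and whether CPB shifts both variables by this much, cannot be settled from the protocol. The documents do not support saying that the plan definitely ignores technique or that it inflates a declared error rate. The absence of a rule for choosing between Pearson and Spearman is a minor matter of clarity.

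**What to change.** In the Statistic section, for ICU admission and every later time point, replace the simple correlations with partial correlations adjusted for technique, or with regression of the marker or outcome on selenium and technique. Show the correlation within each group as well, and analyse each time point separately. The post-induction sample does not need this adjustment on account of CPB.

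As a minor addition, assign one coefficient to each variable type in advance, for example Spearman for scores, durations and skewed markers.

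Technique is already known for every patient, so no new data are needed. Adjustment costs one degree of freedom (97 instead of 98 with 100 patients). The within-group estimates are less precise: with 50 patients the standard error of Fisher's z is 1/√47 = 0.146, against 1/√97 = 0.102 for all 100. They should support the adjusted estimate and not be judged by separate significance.

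Adjustment for haematocrit is not part of this change. It is not among the listed parameters, so adding it would require more than new wording.
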